### Data exclusion criteria

Participants may be excluded based on our predetermined data exclusion criteria, which include the following:

Minimum number of trials after artifact rejection: We determine a preset number of 25 trials per condition as a minimum. Any participant having fewer than 25 trials in any condition after artifact rejection will be excluded from the analysis.Missing information/data: If a participant refuses to complete all or part of the questionnaire about her/his demographic information or the handedness inventory, or if a technical issue leads to missing data/a subset of missing data for a participant, the individual will be excluded from the analysis.Bad channels (1): The threshold for data exclusion is at or over 15% of the electrodes (9 or more) being unusable due to excessive artifacts or environmental noise. This is in the event that these channels cannot be interpolated due to positioning (for example, multiple bad channels being adjacent to each other and therefore not having enough neighbouring electrodes for interpolation).Bad channels (2): A second criterion is if a number of bad channels cluster or are adjacent to one another: If there are 6 bad channels in one cluster/adjacent to one another, the participant will be excluded.Signal-to-noise ratio: As proposed by Parks, Gannon, Long, & Young [44], bootstrap resampling with a value of 9999 bootstraps of ERP waveforms will be used to calculate a signal-to-noise ratio confidence interval for each individual subject (a minimum of 25 trials). The lower bound of this calculation provides an objective measure of signal quality, and ensures that the components we are analyzing exceed a predetermined signal-to-noise ratio. Participants whose signal-to-noise ratio lower bound is below 3.0 dB will be excluded from the analysis. This specific value is within the accuracy peak of subject classification, and experienced ERP investigators have generally considered waveforms below 3.0 dB to be noisy when they are visually inspected.

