### Procedure

Participants will read the participant information sheet, fill out a questionnaire about their demographic details, and sign the informed consent form.

Participants will be seated in front of a presentation monitor on which the sentences will be presented using E-Prime software, and the experiment will start with written instructions that will be explained orally by the experimenter. During the whole experiment, a fixation cross will be shown between trials and sets. Prior to the experiment, participants will be instructed to minimize their head movements during the trials and not to close their eyes while performing the experiment, although they will not be asked to refrain from blinking.

After every 3–8 trials (randomized), participants will be given a comprehension prompt. For the experimental items and filler cleft sentences, the comprehension prompt will be a yes/no question to probe the thematic role assignment (e.g., Did the police shoot the robber?/Did the robber shoot the police?). For the filler questions, the comprehension prompt will be a sentence that appropriately responds to the question (e.g., the adventurer noticed an officer patrolling) or if the noun phrase in the question is presented as the theme (e.g., the officer called the adventurer), and participants will have to judge whether the sentence is an appropriate response to the question (e.g., they should respond "yes" if they see "the adventurer noticed an officer patrolling" after this filler). These prompts are designed to ensure that the participants remain focused and parse the trials displayed, as well as to provide a measure of comprehension performance.

To avoid fatigue, there will be pauses after every block consisting of 30 trials (10 blocks in total), where the participants can take a break and resume the experiment whenever they are ready. The total test session, including cap and electrode preparation, will take approximately one and a half hours per participant.

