### EEG recording and preprocessing

EEGs will be recorded using 64 Ag-Acl electrodes that will be attached to the participant’s scalp via an elastic cap with a 10–20 system. Conductive gel will be used. The cap has two dedicated electrodes for the left and right mastoids. To monitor horizontal and vertical eye movements, two electrodes are fixed in the outer canthi of each eye, and one more will be placed below the left eye (the VEOG above the left eye is integrated in the cap). Electrode impedances will be kept below 5k Ω. The EEG will be amplified and digitized with a sampling rate of 1000 Hz with an analog bandpass filter of 0.03-100Hz. The amplifier that will be used is the SynAmps 2 (NeuroScan, Charlotte, NC, United States), and the cap will be the 64-channel Quik-Cap Neo Net (NeuroScan, Charlotte, NC, United States). Stimtracker (Cedrus) will provide an interface between the experiment presentation software and EEG acquisition. Continuous EEG data will be acquired using Curry 7 acquisition software (Compumedics NeuroScan) whereby the files will be exported to the.cnt format and analysed using EEGLAB [38] for the preprocessing, and FieldTrip [39] for the statistical analysis.

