The EEG data will be re-referenced to the two mastoid electrodes. The ERPs will be calculated per participant, per electrode, and per condition in intervals of 200ms before onset to 1000ms after onset for each time-locked trigger. These epochs will then be demeaned per channel in each epoch (the mean of the data from the entire epoch will be subtracted from each data point, as this may result in better ICA decompositions than baseline-correcting based on pre-stimulus interval; [40]. The epochs will then be subjected to an independent component analysis using the runica() command in EEGLAB [41]; this will divide the data into many independent components corresponding to the number of channels, excluding mastoid electrodes, EOGs, and bad channels that are previously marked. These components will be inspected visually to identify blinks and saccades, and components that are identified as blinks or saccades will be removed (a maximum of four components per participant can be removed, and if the number of components removed exceeds this, the participant will be excluded from the analysis). After the removal of components corresponding to blinks and saccades, baseline correction will be applied to the data with a 200 ms pre-stimulus onset baseline. Next, the epochs will be run through a moving window peak-to-peak threshold function for artefact detection; epochs with artifacts will be marked for removal based on this criterion. Lastly, the data will be filtered using a 0.1–40.0 Hz bandpass filter via the pop_eegfiltnew() default EEGLAB function.

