### Statistical analysis plan

The statistical analysis will be conducted using cluster-based permutation tests [45] over all the scalp electrodes and the entire post-stimulus epoch. The advantage of this approach is that it allows testing for effects anywhere on the scalp and any time in the epoch, while still controlling the familywise false positive rate, and without the experimenter needing to choose regions and time windows for analysis. The test works by comparing the active and passive ERPs at each channel and each sample and identifying clusters of spatiotemporally adjacent data points where the difference between the two conditions exceeds some threshold; in our analysis, that threshold will be two-tailed p < .1 in a t-test. In other words, a t-test comparing active and passive will be performed at every sample in every channel, if a series of several time points in a row on the same channel and/or several adjacent channels at the same time all exceed this threshold, they are treated as a "cluster". Next, each cluster is assigned a test statistic (in our case, the test statistic for a cluster is derived by summing the *t*-values of all the samples in the cluster), and the largest cluster-level test statistic in the epoch is taken as the observed test statistic for the data. Next, the data are randomly permuted (i.e., within each subject, the condition labels "active" and "passive" may be randomly switched) several thousand times, and with each random permutation the abovementioned procedure of identifying clusters and calculating a test statistic is repeated. This yields a permutation distribution of several thousand test statistics, against which the original observed test statistic is compared. The proportion of permutation test statistics that are larger than the original observed test statistic is the *p*-value for the test; if there is a significant difference between the active and passive ERPs then this value will be small. See [45] for a more detailed explanation of how this test works.

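### No exclusion rule uses comprehension-prompt accuracy, although the prompts are the check on parsing and a null result is to be interpreted; the technical-loss and bad-channel rules also need tightening

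*Protocol article*

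**What the plan says.** **Prompts.** Under Procedure, a prompt follows every 3 to 8 trials. For experimental items it asks who did what to whom. The stated purpose is: "These prompts are designed to ensure that the participants remain focused and parse the trials displayed". The prompts are also meant to measure comprehension.

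**Exclusions.** The Data exclusion criteria section describes its rules as predetermined. They cover a minimum of 25 trials per condition after artifact rejection, missing information or data, two bad-channel rules, and a signal-to-noise lower bound of 3.0 dB. EEG recording and preprocessing adds a limit of four removed ICA components. None of these refers to prompt accuracy.

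**Technical loss.** The missing-data rule says: "if a technical issue leads to missing data/a subset of missing data for a participant, the individual will be excluded from the analysis".

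**Bad channels.** The first rule says: "The threshold for data exclusion is at or over 15% of the electrodes (9 or more", where the channels cannot be interpolated. The only electrode count in the article is in "EEGs will be recorded using 64 Ag-Acl electrodes". The test itself is described as "cluster-based permutation tests [45] over all the scalp electrodes and the entire post-stimulus epoch", with no count.

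**Use of a null.** Under Predictions, an absence of ERP differences at both the verb and NP2 is taken to suggest that earlier findings were confounded by syntactic frequency.

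**The concern.** The inference needs readers who assign agent and patient roles to the nouns. The prompts are the only planned evidence that a given participant does so. The trial-count, channel, ICA and signal-to-noise rules measure recording quality, and someone who looks at each word without building the sentence can still give a clean recording.

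Such participants add no voice effect and so move the result towards zero. That matters more here than in a study that interprets only positive findings, because the plan gives the null its own conclusion. The sample of 50 comes from doubling an earlier study's size, not from a power calculation, so no stated margin absorbs dilution.

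Two other rules in the same section are loosely drawn. The technical-loss rule has no stated extent, and the channel rule gives a percentage and a count that do not agree on the only denominator in the article.

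**Working it through.** **1. Is any rule triggered by chance-level answers?** Taking the stated rules in turn:

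- trials remaining: depends on artifacts;
- missing data: depends on refusal or technical faults;
- bad channels (two rules): depends on electrodes;
- signal-to-noise: depends on the waveform;
- ICA components: depends on eye movements.

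None depends on answers. A guesser with a clean recording passes all of them.

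**2. Number of prompts.** Inputs: 10 blocks of 30 trials = 300 trials (Procedure), of which 100 are experimental (Materials), and a gap of 3 to 8 trials.

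- Longest gap: 300 / 8 = 37.5
- Mid-gap 5.5: 300 / 5.5 = 54.5
- Shortest gap: 300 / 3 = 100
- Experimental items at the mid-gap, if prompts are spread in proportion: 54.5 × 100/300 = 18.2

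**3. Could these prompts support a cut-off?** The 70% cut-off and the 90% reader are illustrative assumptions. A guesser is taken as binomial with probability 0.5 and an attentive reader as binomial with probability 0.9.

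| Prompts n | Pass mark (70%, rounded up) | Guesser passes, P(X ≥ mark) | 90% reader fails, P(X < mark) |
|---|---|---|---|
| 37 | 26 | 0.010 | 0.0002 |
| 54 | 38 | 0.0019 | 0.000012 |
| 100 | 70 | 0.00004 | below 0.0000001 |

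An 80%-accurate reader with 54 prompts fails with probability 0.031. If only the 18 or so experimental prompts were scored (pass mark 13), a guesser would pass with probability 0.048, which is a reason to score all prompts.

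**4. Size of the dilution.** If a share f of analysed participants has zero effect and the variance is unchanged, the mean effect is multiplied by 1 − f. For a simple mean difference, the sample size needed rises by 1/(1 − f)².

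- f = 5%: effect × 0.95; N × 1/0.95² = 1.11
- f = 10%: effect × 0.90; N × 1/0.90² = 1.23

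The article gives no value for f. These lines show how dilution scales and are not a forecast.

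**5. Technical loss beside the trial minimum.** With 50 sentences per condition, the 25-trial minimum tolerates artifact loss of 50 − 25 = 25 trials, or 50% of a condition. The technical-loss clause, read literally, tolerates none: one trial lost to a fault excludes the participant.

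**6. The channel figure.** The plan equates 15% with 9 electrodes. On the stated 64, 0.15 × 64 = 9.6, so the first qualifying count is 10 (10/64 = 15.6%), while 9/64 = 14.1%. The article also says "The cap has two dedicated electrodes for the left and right mastoids" and "the VEOG above the left eye is integrated in the cap", and the ICA count is taken "excluding mastoid electrodes, EOGs, and bad channels that are previously marked". Trying the smaller denominators this suggests:

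| Denominator | 9 as a share | First count at or over 15% |
|---|---|---|
| 64 | 14.1% | 10 |
| 62 (less two mastoids) | 14.5% | 10 |
| 61 (less mastoids and cap VEOG) | 14.8% | 10 |
| 60 (assumed) | 15.0% | 9 |
| 58 (assumed) | 15.5% | 9 |

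Nine is the first count at or over 15% only for denominators from 54 to 60, and none of these is stated. The figure is not reproduced from the article; the gap is one channel.

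**The case against.** **The list is open.** It says that participants may be excluded under criteria that include those named, and the ICA limit stands outside it. Prompt performance is measured and can be reported. This stands in part: nothing in the article forbids an accuracy exclusion. But an open list does not supply the rule. It leaves open whether accuracy is used, and that choice could then be made after the ERPs are seen.

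**Few non-parsers are likely.** Participants have first-language or equivalent proficiency and read simple, plausible sentences. This stands. The share of non-parsers may be small and cannot be estimated from the article.

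**Technical loss and artifact loss have different causes.** This stands. A reader might infer that the missing-data rule contradicts the 25-trial minimum. It does not: the minimum counts trials after artifact rejection, and the other rule concerns faults and refusals. What remains is that the technical clause sets no extent.

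**The channel mismatch hardly matters.** This largely stands. It affects only a participant with exactly 9 bad channels that cannot be interpolated, and the second rule already excludes when six adjacent channels are bad. A scalp-only denominator of 60 or fewer would remove the mismatch; the article does not give one.

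**A stronger reading.** A reader might conclude that the analysis will contain the wrong people. The documents do not show this. Two of the three points would, if anything, exclude too many, and no count of affected participants is available. Detectable effect sizes from a single paired t-test would not help either, because the planned analysis is a cluster-based permutation test over all scalp electrodes and the whole post-stimulus epoch.

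**Conclusion.** The point holds in a limited form. The article names the prompts as the safeguard on parsing, interprets a null, and sets no rule by which the prompts affect who is analysed. A chance-level responder with clean EEG therefore passes every stated rule. The direction of the effect is towards the null. Its size depends on an unknown share of non-parsers, and the 5% and 10% figures are assumptions. The planned 38 to 100 prompts separate guessers from attentive readers well, assuming independent answers and one accuracy level per person.

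The technical-loss clause is a secondary point of wording with a possible cost in sample size. The channel threshold is minor: one channel, and close to no participants. This should be settled before data collection, but it does not invalidate the design.

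**What to change.** 1. **Prompt accuracy (main).** Add to the Data exclusion criteria a minimum accuracy over all prompts, fillers included, scored before the ERPs are examined. At least 70% is an example with the error rates shown above; the investigators should choose and justify the value. Report the analysis of all participants, without this criterion, as a sensitivity analysis.
2. **Technical loss (secondary).** Exclude for technical loss only when fewer than 25 clean trials remain in either condition.
3. **Channel rule (minor).** State the denominator and make the percentage and the count agree: with 64 electrodes, 15% is first met at 10; a count of 9 needs a denominator of 54 to 60.

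All three are wording changes that need no extra data collection. The cost of the first is the loss of a few participants, including an occasional genuine but less accurate reader (about 3% of those at 80% accuracy, with 54 prompts).

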### Statistical analysis plan

The statistical analysis will be conducted using cluster-based permutation tests [45] over all the scalp electrodes and the entire post-stimulus epoch. The advantage of this approach is that it allows testing for effects anywhere on the scalp and any time in the epoch, while still controlling the familywise false positive rate, and without the experimenter needing to choose regions and time windows for analysis. The test works by comparing the active and passive ERPs at each channel and each sample and identifying clusters of spatiotemporally adjacent data points where the difference between the two conditions exceeds some threshold; in our analysis, that threshold will be two-tailed p < .1 in a t-test. In other words, a t-test comparing active and passive will be performed at every sample in every channel, if a series of several time points in a row on the same channel and/or several adjacent channels at the same time all exceed this threshold, they are treated as a "cluster". Next, each cluster is assigned a test statistic (in our case, the test statistic for a cluster is derived by summing the *t*-values of all the samples in the cluster), and the largest cluster-level test statistic in the epoch is taken as the observed test statistic for the data. Next, the data are randomly permuted (i.e., within each subject, the condition labels "active" and "passive" may be randomly switched) several thousand times, and with each random permutation the abovementioned procedure of identifying clusters and calculating a test statistic is repeated. This yields a permutation distribution of several thousand test statistics, against which the original observed test statistic is compared. The proportion of permutation test statistics that are larger than the original observed test statistic is the *p*-value for the test; if there is a significant difference between the active and passive ERPs then this value will be small. See [45] for a more detailed explanation of how this test works.

We will run the test using a cluster threshold of *p* < .1, as this makes the test more sensitive to weak, sustained effects similar to what was found in previous studies that have investigated thematic role processing (see [45], for discussion of how the cluster threshold influences the sensitivity of the test to different types of effects) and at least two spatial neighbouring electrodes that also meet the threshold (we will use the *minnbchan = 2* function in the Fieldtrip implementation of the cluster-based test). The permutation test will use 5000 iterations.

## Predictions

There are several possible patterns of the results. These are described below.

An ERP contrast can be expected between canonical and non-canonical sentences on the critical region (verb). We can expect a posterior positivity (P600) at the disambiguation point to indicate that a revision of the thematic information is needed: NP1 should be reassigned from the default agent role to become the patient of the action.An ERP contrast can be expected between canonical and non-canonical sentences in the NP2 time windows. Additionally, based on earlier studies we expect a ‘generalized’ increase in processing costs in comprehending the non-canonical structures attributed to violation of transitivity expectation [16] as well as retrieval of verbal material in a non-canonical position and uptick in working memory demands [19]. For example, the verbs in Basque [19] and Japanese [16] provide no additional thematic information, but within that section, ERP differences for object-first compared to subject-first structures were observed.A lack of ERP correlates in both the verb and NP2, especially between the passive and active conditions, suggests that previous findings regarding the neural correlates of thematic role assignment were confounded by syntactic frequency because the studies compared one highly frequent structure (e.g. active) to a highly infrequent sentence structure (e.g. passive).

In general, for the time windows and specific components, due to the nature of cluster-based permutation where adjacent sites and time points are correlated, we will be looking at the whole epoch (here we theorize that a ‘real’ effect should persist through multiple adjacent electrodes and a chunk of tens to hundreds of milliseconds/samples–a more detailed description of the procedure is provided by [45]). However, were there to be an effect in either the verb or NP2 (as per the predictions above), we expect it to be observed in the time windows and distributions corresponding to the LAN, N400, and/or P600 –all of which have been observed in similar studies and above 300ms. Specifically, for the verb, we would expect the passive to be more positive than the active for the 500-700ms time window, as this was what the study closest [15] to this one reported in their critical region. For NP2, we expect some form of negativity to occur for the passive compared to the active between the 300-600ms time window–this was observed in studies which reported ERPs post-disambiguation.

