## Abstract

Previous studies of multiple languages have found processing differences between patient-first and agent-first word orders. However, the results are inconsistent as they do not identify a specific ERP component as a unique correlate of thematic role processing. Furthermore, these studies generally confound word order with frequency, as patient-first structures tend to be infrequent in the languages that have been investigated. There is evidence that frequency at the sentence level plays a significant role in language processing. To address this potential confounding variable, we will test a language where the non-canonical sentences are more frequent and are comparable to the canonical sentences, namely Standard Indonesian. In this language, there is evidence from acquisition, corpus, and clinical data indicates that the use of passive is frequent and salient. One instance of this difference can be demonstrated by the fact that it has been suggested that frequency may be the reason why Indonesian-speaking aphasic speakers do not have impairments in the comprehension of passives, whereas speakers of other languages with aphasia often do. In the present study, we will test 50 native speakers of Indonesian using 100 sentences (50 active and 50 passive sentences). If the neural correlates of thematic role processing are not observed in the critical region of the sentence (the prefix of the verb), this would suggest that the previous results were indeed influenced by frequency, but if we find that specific ERPs are connected to the hypothesized syntactic operations, this would further reinforce the existing evidence of the increased cognitive load required to process more syntactically complicated sentences.

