Other studies which have investigated thematic role assignment processing through ERPs included Meltzer and Braun [10], who compared the processing difference between subject-embedded and object-embedded relative clauses in English, and they found a negativity at NP1 (400-800ms) and a positive shift at the offset of the relative clause for reversible clauses. Jackson, Lorimor, & van Hell [15] observed positivity at the 500-700ms time window when comparing English passive structures to active structures; this positivity was strongest at the left anterior electrodes. In a study of Japanese, Wolff, Schlesewsky, Hirotani, and Bornkessel-Schlesewsky [16] included sentences that were similar to those in German, in which the object-first structures were compared to subject-first structures via the use of a suffix in the nominative or accusative case on the NP. ERPs for object-initial compared to subject-initial structures after NP1 included an early (120-240ms) negativity, which was referred to as ‘scrambling negativity’, a broadly distributed positive shift at the NP1 of Object-Subject structures (400-650ms), an N400 at the NP2 for Subject-Object structures, and a late parietal negativity (650-1050ms) at the verb. Aside from the object scrambling, the positive shift at the NP1 in object-initial sentences was interpreted as the resolution of dependency introduced by an accusative-first argument. Another study on Japanese [17] investigated how context usage influences processing of object-first structures. They observed that object-first structures elicited a sustained LAN at NP1 and P600 at NP2 when the NP1 was new and not provided in the context.

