For case-marking languages, there appears to be a pattern of a negative shift in NP1, which is the critical region of the sentence for thematic role assignment. However, other parts of the sentence indicate a different pattern: The P600 found in both Basque [19] and English [15] verbs is somewhat contradictory, as the case information denoting the thematic role assignment was provided earlier at the NP1 in Basque; as such, this P600 cannot be attributed to thematic role processing, and the authors attributed it to ‘higher syntactic complexity’. By contrast, a study of Japanese [16] found a late negativity on the verb, which was an effect in a similar time window but with opposite polarity. Due to the inconsistencies in these findings (which may be in part attributed to the experimental design and the languages examined in these studies), it is particularly difficult to draw a conclusion on what constitutes a neural correlate of thematic role processing. To summarize the findings of comparable studies, Table 1 outlines the results of the discussed literature with results from [10] presented separately as unlike the other studies, they discuss relative clauses with different regions measured.

**Table 1 pone.0272207.t001:** Summary of previous ERP studies comparing word orders.

Language	Conditions	NP1	NP2	V	Note
German* [12]	SVO-OVS	LAN (400-600ms, 600-800ms)	- Negativity (400-1000ms)	Not discussed	Nom/Acc case was provided by articles preceding NPs.
	Ambiguity (fem. NP1 vs masc. NP1)		- P600 (600-800ms, 800-1000ms) for amb. fem. NP1		
Japanese* [16]	SOV-OSV	- Scrambling negativity (120-240ms)	N400 (300-500ms)	Late negativity (650-1000ms)	Nom/Acc case was provided by markers following the NPs.
		- positivity (400-650ms)			
Basque* [19]	SOV-OSV	Negativity (300-500ms)	Negativity (400-550ms)	P600 (700-900ms)	Erg/Abs case was provided by markers following the NPs.
English* [15]	Act-Pas	Not discussed	Not discussed	P600 (500-700ms)	Frontal distribution of P600- different from the typical distribution in garden-path sentences.
	Conditions	NP1	RC onset	RC offset	
English [10]	S.RC–O.RC	Negativity (400-800ms) for reversible	Not found	positivity (-300-100ms)	Only found reversibility effects, no word order effect.
	Reversibility	(i.e. ani. NP1 vs inani. NP1)		for rev. conditions	

*all components are evoked to compare object-first to subject-first structures

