### The present study

The current study will investigate the processing of non-anomalous, simple sentences with differing word orders. The focus will be on the critical point in time, which is mainly the verb, but other regions of the sentence (such as NP2) will be investigated to check for spill-over effects.

The two conditions to be included are the active and the passive. The materials will be typical, plausible, reversible (both noun phrases are animate), violation-free sentences. There are some aspects of the Indonesian language that make the topic of the present study worth pursuing. First, the thematic roles of the NPs are coded by the passivization prefix on the verb rather than by case marking on the NPs. Second, unlike the studies of German [12] and Basque [19], no ambiguity manipulations are involved. Third, the structures to be tested in the current study are both relatively frequent compared to the passive structures in previously studied languages and are considered to be typical. The object-first conditions in the previous studies are infrequent in the respective languages compared to their subject-first counterparts; for example, the object-embedded relative clause in English [26] and the object-subject structure in German [27] are both highly infrequent structures. While arguments against exclusively syntactic frequency-based accounts of sentence processing have been established for German [28], there is behavioral evidence of the influence of sentence-level frequency and its interaction with other syntactic contrasts, such as the lexical bias of verbs [29–31].

The current experiment will contribute by providing electrophysiological data from Standard Indonesian, a zero-marking language that lacks many morphosyntactic features of Indo-European languages, paired with a relatively rigid word order. To the best of our knowledge, no ERP study has investigated Indonesian, where the ‘non-canonical’ sentence structure is relatively frequent. This is important because all the previous studies have compared one common sentence structure to an extremely infrequent one, and there is a wealth of evidence suggesting that syntactic frequency plays a role in sentence processing at the behavioral level [2, 32, 33].

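### A null at the verb and NP2 could not be attributed to syntactic frequency, because across most of the earlier studies frequency changes together with construction and role marking

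*Protocol article*

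**What the plan says.** The third prediction in the Predictions section states that a lack of ERP effects at both the verb and NP2 "suggests that previous findings regarding the neural correlates of thematic role assignment were confounded by syntactic frequency". The Abstract gives the same reading for a null at the verb prefix: "this would suggest that the previous results were indeed influenced by frequency". Neither place offers another explanation of a null.

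The section The present study lists three features that set this experiment apart from earlier work. On marking, "the thematic roles of the NPs are coded by the passivization prefix on the verb rather than by case marking on the NPs". On ambiguity, "unlike the studies of German [12] and Basque [19], no ambiguity manipulations are involved". On frequency, "the structures to be tested in the current study are both relatively frequent compared to the passive structures in previously studied languages". The same section gives the premise behind the null reading: "all the previous studies have compared one common sentence structure to an extremely infrequent one".

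The Frequency section accepts that the relative frequency of a structure in a language may not be open to manipulation. What it controls is verb-level frequency, through the choice of verb pairs.

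**The concern.** The null reading credits one of three listed differences and leaves out the other two. Table 1 adds a fourth, the construction being contrasted. If frequency moves together with these features from the earlier studies to this one, a null cannot tell them apart, however convincingly it is established. This is separate from the question of whether a non-significant cluster test shows absence of an effect.

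At stake is what the study may conclude. The article is a Registered Report Protocol, so its interpretations are set before data are seen. As worded, a null would be taken to bear on earlier findings in general, including effects in case-marked sentences at a region where the Indonesian design has no contrast.

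**Working it through.** The plan attaches no figure to this inference, so there is none to reproduce. The check is a tally of the comparator studies and a comparison of sections.

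**1. Inputs.** Contrast and marking come from Table 1 and its notes. Ambiguity comes from The present study, which names German and Basque only. Each study is scored 1 if it differs from the Indonesian active-passive contrast on that feature.

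| Study in Table 1 | Contrast | Construction differs | Roles marked by case on NPs | Ambiguity manipulation named |
|---|---|---|---|---|
| German | SVO-OVS | 1 | 1 | 1 |
| Japanese | SOV-OSV | 1 | 1 | 0 |
| Basque | SOV-OSV | 1 | 1 | 1 |
| English | active-passive | 0 | 0 | 0 |
| English | subject vs object relative clause | 1 | 0 | 0 |

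**2. Counts.**
- Construction: 1 + 1 + 1 + 0 + 1 = 4 of 5.
- Marking locus: 1 + 1 + 1 + 0 + 0 = 3 of 5.
- Ambiguity: 1 + 0 + 1 + 0 + 0 = 2 of 5.
- At least one of the three: 4 of 5.
- All three: 2 of 5 (German and Basque).

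**3. Where frequency varies.** Some relevant properties of Standard Indonesian gives passive input frequencies of 28–35% for Indonesian and 4–5% for English. Assuming every non-passive is active, the active:passive ratio is (1 − p)/p:
- Indonesian: 0.72/0.28 = 2.57 down to 0.65/0.35 = 1.86.
- English: 0.96/0.04 = 24 down to 0.95/0.05 = 19.

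The between-language difference is large, so frequency is a reasonable candidate explanation. But it exists only between languages. The study has one language, two conditions, and no infrequent comparison structure, so nothing in it varies structural frequency while holding construction and marking fixed.

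**4. Regions.** Table 1 records NP1 effects in all three case-marked studies (German, Japanese, Basque), and the accompanying text treats NP1 as the region where roles are assigned in such languages. In Indonesian the roles are marked on the verb, and in the Table 2 example NP1 is the same noun in both conditions. Materials uses NP1 data only as a sanity check for baseline differences. The planned null covers the verb and NP2. It therefore has no counterpart to the earlier NP1 effects.

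**5. Caveats not carried forward.** The section on word order processing says that inconsistent earlier findings may be partly due to design and language. The present study acknowledges arguments, established for German, against accounts based only on syntactic frequency. Neither caveat reaches the null reading in Predictions or the Abstract.

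**The case against.** The plan's wording is hedged. It says that a null suggests confounding, or that earlier results were influenced by frequency; it does not say frequency was the sole cause. A reader might infer that the plan would declare the German, Japanese and Basque results to be frequency artefacts, but it does not say so, and its bracketed examples are active and passive. That much stands. The hedge limits the strength of the claim, though, not its scope, which is earlier findings in general.

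The closest comparator, the English active-passive study, shares construction and verb-region coding. There the objections about marking, construction and ambiguity largely fall away, and a frequency reading is most defensible. Some reservation remains: the language differs, and the Frequency section itself flags the progressive form used in that study as a possible separate source of signal.

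A reader might go further and say that a null has no bearing at all on the case-marked studies. The document does not support that. The second prediction ties NP2 to the Basque and Japanese verb effects, which arise after the roles are already known, so a null at NP2 has some relevance to those.

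Nor does ambiguity separate this study from most earlier ones. Only two of five are named, and the German sentences with masculine NP1 showed a left anterior negativity outside the ambiguous condition.

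Finally, the broad reading of a null could be left to the discussion of the results paper. In a registered report, however, the reading is being fixed now.

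**Conclusion.** The concern holds in this limited form: the design cannot attribute a null to syntactic frequency as the confounder of earlier findings in general. Four of the five tabulated studies differ in at least one feature other than frequency, and two differ in all three features counted. No inference about the NP1 effects of the case-marked studies is available. A null remains compatible with a contribution of frequency, most directly for the English active-passive effect at the verb. The tally rests on the article's own descriptions of those studies.

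It is tempting to add that Table 1 already refutes a frequency account, because The present study calls the English object relative clause highly infrequent while Table 1 says of that study: "Only found reversibility effects, no word order effect". The documents do not support that step. One such result shows only that low frequency did not suffice to produce an effect there; confounding does not require every infrequent structure to produce one. The article also sets this study apart because different regions were measured. And it contradicts itself: the section on word order processing cites the same study among those that documented word-order differences. The two statements need reconciling.

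**What to change.** In the Abstract and in the third prediction:

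- State that a null at the verb and NP2 would be compatible with frequency having contributed to earlier effects, most directly the English active-passive effect at the verb.
- State that for the case-marked object-first studies, marking locus and construction (and, for German and Basque, ambiguity) remain competing explanations that the design does not exclude.
- State that no inference will be drawn about the NP1 effects in those studies.

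Separately, reconcile the text of the word order section with the Table 1 entry for the relative-clause study. Do not cite that study as evidence against frequency.

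The cost is wording only: no change to sample, stimuli, test or exclusions. The downside is a narrower headline claim.
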